### Statistics

An audit at a Danish University Hospital of all their primary vaginal deliveries from 2003 to 2011 (*n* = 15,587) found that 86% sustained a perineal tear [3]. The hypothesis of this trial is that primary delivery of the posterior shoulder can reduce the incidence of perineal tears, and that a reduction of 10% is clinically significant. It is assumed that the rate of perineal tears using the traditional method of delivering the anterior shoulder first is 85%. The sample size calculation for the primary outcome is based on a minimal relevant difference in the proportions of perineal tears between the two intervention groups of 10%, with 80% power and a significance level of 0.05. Thus, we estimated that 250 women would have to be included in each intervention arm. In Denmark, 18% of primiparous women had an acute Cesarean section in 2011 [20]. Because of this probability of acute Cesarean section and the likelihood of drop-outs, 650 women will be included in this trial.

At the University of Copenhagen, Holbæk Hospital, 840 children were delivered by primiparous women in 2011. With an inclusion rate of 80% and assessment starting in January 2013, it is estimated that randomization can be finalized before December 2014.

All included women delivering vaginally will be included in the final analysis. The analysis will primarily be based on an intention-to-treat principle. It will be supplemented with a per-protocol analysis (of the women who received their random allocation) and an as-treated analysis (according to how the shoulders were actually delivered). Categorical variables, including the primary outcome, will be analyzed with the chi-squared test or Fisher’s exact test as appropriate, and the odds ratios presented with 95% confidence intervals. Continuous variables will be assessed for normal distribution with the Kolmogorov-Smirnov test. When normally distributed, they will be analyzed with a *t* test, and when not, with a Mann-Whitney test.

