## Background

Approximately 85% of vaginal deliveries are accompanied by trauma to the genital tract, with a higher risk at the first compared with subsequent vaginal births [1,2]. Among primipara with vaginal deliveries, 86% sustain a vaginal or perineal tear, and 77% require suturing of a lesion [1,3].

Birth trauma is associated with both short- and long-term morbidity, including pain, discomfort, dyspareunia and fecal incontinence, and perineal trauma may cause social problems and affect the psychological well-being of the mother [1,4]. The level of postpartum morbidity is related to the degree of trauma [5,6], and studies of preventive measures are therefore of interest.

Genital tract traumas are classified into subtypes according to the location and severity of the lesion. Most studies have evaluated the risk factors for third- and fourth-degree perineal tears that include the anal sphincter complex, so-called obstetric anal sphincter injuries (OASIS). Predisposing factors are increasing maternal age, heavier birthweight, longer duration of the second stage of labour, oxytocin augmentation, occiput posterior position and instrumental delivery [7-9]. The risk increases with the number of different risk factors [9]. Protective factors are previous vaginal delivery, epidural analgesia and multiparity [7-9]. Several perineal management techniques used during delivery have been studied, and a recent Cochrane review concluded that warm compresses and perineal massage seem to reduce the risk of OASIS [4]. The introduction of an interventional perineal protection programme also seems to reduce the incidence of OASIS [10-12].

Leading textbooks recommend primary delivery of the anterior shoulder by gentle traction if the shoulders are not delivered spontaneously [13,14]. However, if shoulder dystocia occurs, the recommended manoeuvres are primary delivery of the posterior arm or primary delivery of the posterior shoulder, with the woman positioned on her hands and knees (Gaskin’s manoeuvre) [15,16]. A computer-simulated trial of the manoeuvres used during shoulder dystocia found that primary delivery of the posterior arm caused an 80% reduction in the delivery force and a 70% reduction in stretch to the brachial plexus [17]. Primary delivery of the posterior shoulder could therefore be of advantage during uncomplicated deliveries, but, to the knowledge of the authors, various methods of shoulder delivery have never been studied previously.

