### Participants

Eligible participants are primiparous women and women with one previous Cesarean section, who are planning a vaginal delivery of a fetus in cephalic presentation. Patients have to be able to provide informed oral and written consent. Exclusion criteria are multiparity with a previous vaginal delivery, multiple pregnancy, acute or planned Cesarean section, delivery before 35 weeks of gestation, and breech delivery.

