### Outcomes

The primary outcome is any perineal trauma. Secondary outcomes are the perineal injury subtypes, postpartum bleeding in millilitres evaluated 2 hours after birth, umbilical artery pH, Apgar scores at 5 minutes and neonatal birth trauma, including fractures of the clavicle and humerus, and brachial plexus injury.

Perineal traumas are classified as anterior or posterior, and posterior traumas are classified into subtypes. Anterior trauma comprises lacerations of the labia that do or do not require suturing. Posterior subtypes comprise lacerations of the vagina and/or perineum that do not require suturing; first-degree tears, where only the skin or mucosa is involved (1A: <1.5 cm; 1B: ≥1.5 cm); second-degree tears, where skin and perineal muscle is involved with the anal sphincter intact but not visible (2A) or visible (2B); third-degree tears involving the anal sphincter complex (3A, less than 50% of the external anal sphincter is torn; 3B, 50% or more of the external anal sphincter is torn; 3C, both the internal and external anal sphincters are torn); and fourth-degree tears involving the anal sphincter complex as well as anal epithelium [18,19].

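### The primary comparison is a valid unadjusted test, but prespecified adjustment for maternal age and birthweight would be a cheap improvement of uncertain size

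*Protocol article*

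**What the plan says.** In the protocol article, Statistics, the test is fixed directly: "Categorical variables, including the primary outcome, will be analyzed with the chi-squared test" or, where suitable, Fisher's exact test, with odds ratios and 95% confidence intervals. Intention to treat is primary, and per-protocol and as-treated analyses supplement it. No covariate enters any of them. Under Outcomes, "The primary outcome is any perineal trauma", a yes/no variable that takes in every grade from unsutured lacerations to fourth-degree tears.

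The Randomization section describes computer-generated 1:1 allocation and mentions no stratification. Women are randomized on arrival at the delivery ward, and the midwife opens the envelope at the start of the second stage.

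The Background gives a list of risk factors: "Predisposing factors are increasing maternal age, heavier birthweight, longer duration of the second stage of labour", followed by oxytocin augmentation, occiput posterior position and instrumental delivery. It introduces them as risk factors for third- and fourth-degree tears and gives no effect sizes.

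**The concern.** When some women are at higher risk of the outcome for reasons unrelated to allocation, a comparison that ignores those reasons stays valid but is somewhat less precise than one that uses them. Any chance difference between the arms, for example heavier babies in one of them, also stays in the estimate. Maternal age is fixed before randomization. Birthweight is measured afterwards, but the order of shoulder delivery cannot alter it. Both can therefore be adjusted for safely.

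At stake are a few points of power at most, a slightly narrower interval for the risk difference, and a ready answer if a borderline result is attributed to imbalance. An adjustment chosen once the results are known would look selective.

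**Working it through.** **1. The plan's own figure.** Inputs from Statistics: control rate 85%; a "minimal relevant difference in the proportions of perineal tears between the two intervention groups of 10" per cent, read as percentage points, so 75% in the other arm; "with 80% power and a significance level of 0.05", taken as two-sided. With mean rate 0.80,

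n = [1.960 × √(2 × 0.80 × 0.20) + 0.8416 × √(0.85 × 0.15 + 0.75 × 0.25)]² / 0.10² = (1.1087 + 0.4724)² / 0.01 = 249.98.

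The stated 250 per arm is reproduced, by the same unadjusted comparison as the planned test.

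**2. Reserve in the enrolment.** 650 × (1 − 0.18) = 533 vaginal deliveries, about 266 per arm, which gives 82.4% power before drop-outs. The protocol puts no figure on drop-outs. Power returns to 80% if a further 33 women (533 − 500) are lost.

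**3. Gain by formula.** Let R² be the share of outcome variance that the covariates explain. Adjustment multiplies the variance of the risk difference by about 1 − R². At 250 per arm the unadjusted half-width of the 95% CI is 1.96 × √(0.315 / 250) = 6.96 points. R² is an assumption, because the documents give no value:

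| R² | Power | CI half-width (points) |
|---|---|---|
| 0 | 80.0% | 6.96 |
| 0.02 | 80.8% | 6.89 |
| 0.05 | 82.0% | 6.78 |
| 0.10 | 84.0% | 6.60 |
| 0.20 | 88.0% | 6.22 |

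**4. Gain by simulation.** 4,000 trials per setting, 250 per arm, marginal rates held at 85% and 75%, one standard normal covariate. The chi-squared test is set against the test of allocation in a logistic model with the covariate. The last column is the SD of the estimated risk difference in percentage points, crude and then standardised from the model.

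| Odds ratio per SD (assumed) | R² | Power, unadjusted | Power, adjusted | SD of risk difference |
|---|---|---|---|---|
| 1.3 | 0.01 | 81.1% | 81.3% | 3.51 → 3.49 |
| 1.5 | 0.02 | 80.2% | 81.0% | 3.54 → 3.51 |
| 2.0 | 0.06 | 80.1% | 83.3% | 3.54 → 3.40 |
| 3.0 | 0.14 | 80.0% | 85.4% | 3.63 → 3.34 |

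The Monte Carlo standard error of each power figure is √(0.8 × 0.2 / 4000), about 0.6 points. Type I error, including a setting with no covariate effect, was 4.4% to 5.6% unadjusted and 4.6% to 5.5% adjusted.

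**5. The scale matters.** The crude odds ratio is (0.75/0.25) / (0.85/0.15) = 0.529. In the adjusted logistic model the standard error of the log odds ratio rises from 0.231 to 0.235, 0.241 and 0.253 (odds ratio per SD 1.5, 2.0, 3.0), while the conditional odds ratio moves away from 1, to 0.521, 0.505 and 0.472. The power gain is real, but the coefficient is a different quantity with a wider log-scale interval. A standardised estimate keeps the original estimand, and its variability falls, as the last column in step 4 shows.

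**6. Chance imbalance.** At 250 per arm a standardised covariate difference has standard error √(2/250) = 0.0894. A difference of 0.15 SD or more has z = 0.15 / 0.0894 = 1.68, so it occurs in about 9% of trials for any one covariate.

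**The case against.** The strongest reply is that nothing is wrong. The planned test is valid, keeps its type I error, delivers its stated power and matches the sample-size calculation. A supportive adjusted analysis may also sit in an analysis plan that is not shown. All of that stands, and it limits the point to an efficiency improvement. The point remains because the article positively assigns the primary outcome to an unadjusted test.

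Three stronger readings are tempting, and the documents do not support them.

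- **That the protocol lists strong predictors of the primary outcome.** The list concerns third- and fourth-degree tears and has no effect sizes. The primary outcome is much broader and is expected in about 85% of women. For trauma overall the Background names only first against subsequent vaginal birth. Eligibility largely removes that factor: "Eligible participants are primiparous women and women with one previous Cesarean section", with previous vaginal delivery excluded. A gain near zero is as compatible with the documents as one of 5 points.
- **That the trial has no reserve.** 250 per arm is the number required, not the number enrolled; see step 2.
- **That the gain costs nothing.** Ordinary logistic adjustment changes the estimand (step 5), and the covariates have to be available. Reporting a standardised effect answers the first of these, but such an estimate needs explaining.

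Nor are all the listed factors suitable. Second-stage duration and instrumental delivery follow the opening of the envelope, and oxytocin may start after randomization.

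**Conclusion.** The point holds as a cheap improvement to a stated method. The expected gain is about 0 to 1 power point if age and birthweight are weak predictors of any perineal trauma, and about 3 to 5 points if they are strong, with type I error unchanged and some protection against chance imbalance. The range rests on assumed covariate strengths, on 250 analysed women per arm and on true rates of 85% and 75%. No definite loss can be attributed to the present plan, and a result from the planned chi-squared test would be sound.

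**What to change.** Before the allocation is broken, prespecify the primary intention-to-treat comparison as a logistic model with allocation, maternal age and birthweight, both covariates continuous. Report the covariate-standardised (marginal) risk difference and marginal odds ratio with 95% CI, and name the variance method. Keep the chi-squared or Fisher test with the crude odds ratio as the supporting unadjusted analysis. State that second-stage duration, oxytocin, instrumental delivery and episiotomy are not adjusted for, because they can arise after randomization or after the midwife knows the allocation.

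The cost is a sentence or two in the analysis section, a few lines of code, and an amendment by the route described under Ethical consideration; the trial was still recruiting at publication. It assumes that both covariates can be taken from the birth record. The standardised estimate will need a short explanation in the report.

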### Ethical consideration

Gentle traction is recommended to deliver the shoulders during vaginal birth, and there is no available evidence of which shoulder should be delivered first. There is therefore no increased risk involved for the women included in the trial, while an increased focus on preventing perineal trauma through the trial may be advantageous for the participants. The results of the trial will improve future birthing care.

The trial complies with the current version of the Declaration of Helsinki on biomedical research. The trial is approved by the regional ethics committee for Region Zealand (registration number SJ 310) and is registered with ClinicalTrials.gov (registration number NCT01937546).

All included women will give written informed consent confirming that they have received adequate written and oral information. Trial participants do not receive any financial compensation.

We followed the SPIRIT (Standard Protocol Items: Recommendations for Interventional Trials) guidelines for writing clinical trial protocols [21]. The latest version of the trial protocol is available in Danish on the trial website [22]. Any amendments to the trial protocol have to be accepted by the regional ethics committee.

The results of the trial will be disseminated through presentation at international conferences and will be published in an international peer-reviewed medical journal regardless of magnitude and direction of effect. The authors of this protocol will co-author the final trial report. All authors of the final trial report will adhere to the criteria of the International Committee of Medical Journal Editors [23]. After publishing the final trial report, the final results of the trial will be published in Danish on the trial website, where the final trial report will also be made available.

## Discussion

The purpose of this randomized controlled trial is to compare two methods of delivering the shoulders during vaginal delivery, with perineal trauma as the primary outcome.

The literature on delivery techniques is limited, and previous studies have primarily focused on their effect on OASIS. Most studies have been non-randomized, and different shoulder delivery techniques have not been evaluated previously. Thus, the strengths of this study are the randomized design, the intervention studied, that is, the delivery of the shoulders at vaginal delivery and the outcome of any perineal trauma.

The validity of this trial could be affected by the fact that several midwives perform the interventions. However, numerous birth assistants are a reality at most centres, thereby increasing the external validity and generalizability of the trial. Additionally, it might be interpreted as a limitation that this is a single-centre trial, although it increases internal validity of the trial. The perineal tears are evaluated by several objective assessors (midwives or doctors), which might possibly affect the validity of the outcome assessment. We will try to overcome this issue by validating registered higher-degree tears (third- and fourth-degree) by examining patient records. Additionally, we are planning to retrieve data on all third- and fourth-degree tears in our study population during the study period from the hospital registers and validate these data against patient records. We assume that higher-degree tears, in particular, may be diagnosed after trial assessment. These tears will be registered centrally because registration commonly takes place after lesion repair. Thus, all higher-degree tears included in our final analysis will be validated.

Most delivery assistance techniques used today are based on tradition and heritage and are not evidence-based. This trial provides an example of how vaginal delivery techniques may be evaluated in a randomized controlled trial.

The results of this trial will clarify the role that delivery of the shoulders has on perineal trauma and thereby provide knowledge to recommendations on birthing technique.

## Trial status

Recruitment commenced in January 2013, and the first included patient delivered in June 2013. The trial is currently recruiting.

## Abbreviations

OASIS: obstetric anal sphincter injuries; SPIRIT: Standard Protocol Items: Recommendations for Interventional Trials.
